#### 2.2.2. Sample Size Calculation

The sample size was determined a priori through power analysis using GPower 3.1 [28], targeting the primary statistical test: a mixed-model ANOVA with 2 between-subjects groups (Vax vs. No-Vax), and 2 within-subjects factors—stimulus (CS+ threat-associated stimulus vs. CS− safety-associated stimulus) and time (3 SCR measurements: habituation, acquisition, extinction recall). The analysis aimed to detect a medium effect size (f = 0.25), with 95% power at an alpha level of 0.05. A moderate correlation of r = 0.5 was assumed among the six repeated measurements (2 stimuli × 3 phases), based on prior psychophysiological research and expected consistency in responses influenced by individual differences in disgust sensitivity and anxiety. This correlation was explicitly specified in GPower to ensure accurate estimation. Under the assumption of ideal sphericity (ε = 1), a minimum of 40 participants is required.

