Following the completion of demographic and psychological questionnaires, participants will be immersed in a virtual reality (VR) environment for a Pavlovian fear conditioning and extinction task created by our group [45,46]. The paradigm consists of three phases—habituation, acquisition, and extinction, conducted over one day. During habituation, participants will observe two colored doors (blue and red) presented in a randomized order across eight trials. In the acquisition phase, the blue door (CS+) will be paired with an aversive stimulus—an approaching, screaming monster (80 dB)—in 80% of trials, while the red door (CS−) will not be associated with any aversive event. Ten minutes after acquisition, the extinction phase will begin. During this phase, the blue door (CS+) will no longer be followed by the aversive stimulus, allowing participants to experience its diminished threat value. Extinction will last approximately ten minutes and contain 20 trials. The recall session will occur 24 h later, during which the same blue door (CS+) will again be presented without any aversive stimulus. Throughout the experiment, participants will rate the perceived fearfulness of each stimulus using a 10-point Likert scale (1 = not scary at all; 10 = extremely scary). Typical CS− and CS+ sequences during the acquisition phase can be found in Lucifora et al. [47]. Participants scoring high on the State-Trait Anxiety Inventory will be excluded from the experiment.

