### 2.8. Statistical Methods

All statistical analyses will be conducted using Jamovi (version 2.6.23), an open-source statistical software based on the R 4.5.0 framework. A significant threshold of *p* < 0.05 will be applied to all analyses. Parametric methods will be employed under the assumptions of normality and homogeneity of variance, verified by Shapiro-Wilk or Kolmogorov-Smirnov and Levene’s tests, respectively. Non-parametric tests will be used if assumptions are violated.

#### 2.8.1. Experiment 1

A 2 × 2 × 3 mixed-design ANOVA will be conducted to analyze differences in MEP amplitudes, with group (Vax vs. No-Vax) as a between-subjects factor, muscle (deltoid vs. extensor carpi radialis), condition (Blood, COVID-19, influenza), as within-subjects factors.

EMG activity from the levator labii superioris (disgust) and corrugator supercilii (fear) will be analyzed using a 2 × 2 × 3 mixed-design ANOVA, incorporating group (Vax vs. No-Vax), muscles (levator labii superioris, corrugator supercilii), condition (Blood, COVID-19, influenza).

Significant interactions (*p* < 0.05) will be followed by Tukey’s HSD post hoc tests to identify condition-specific effects.

#### 2.8.2. Experiment 2

Habituation, fear acquisition, extinction, and recall will be assessed through Skin Conductance Response (SCR) amplitudes using a 2 × 2 × 3 mixed-design ANOVA. The analysis will compare responses to stimuli (CS+ threat-associated stimulus, CS− safety-associated stimulus) as a within-subjects factor, across groups (Vax vs. No-Vax) as a between-subjects factor and phases (habituation, fear acquisition, fear extinction) as a within-subjects factor. Similarly, subjective fear/disgust ratings (Likert scale) will be analyzed using a 2 × 2 × 3 mixed-design ANOVA, with group (Vax vs. No-Vax) as a between-subjects factor, and stimulus Type (CS+ vs. CS−) and phase (habituation, fear acquisition, fear extinction) as within-subjects factors. Significant interactions (*p* < 0.05) will be followed by Tukey’s HSD post hoc tests to identify condition-specific effects.

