Through the Pavlovian fear conditioning and extinction paradigm, we expect vaccine-hesitant individuals to exhibit higher skin conductance responses (SCR) to the conditioned stimulus (CS+), indicating exaggerated fear responses during the acquisition phase. Furthermore, we anticipate a lower extinction learning, leading to increased fear retention during the recall session. Such findings would suggest that vaccine-hesitant individuals exhibit altered patterns of threat updating, which could be associated with the persistence of avoidance-related behaviors. These results would align VH with other avoidance-based behaviors, emphasizing the need for interventions targeting fear extinction [22,54]. Consistent with previous research, we anticipate that specific psychological traits will be significantly associated with higher levels of VH. Higher scores in disgust sensitivity, paranoia, and dogmatic thinking are expected to be associated with increased VH. These findings would further emphasize the complex interplay between cognitive rigidity, emotional processing, and vaccine decision-making [19,20,55].

In conclusion, this protocol will have significant public health implications by advancing our understanding of the psychophysiological mechanisms underlying VH. It will offer valuable insights for future pandemics and help develop tailored public health messages that integrate sociocultural, clinical, and neurobiological factors.

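### Experiment 2's phase factor is defined in two incompatible ways, and with the levels listed in the analysis section no specified analysis tests the recall prediction

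*Protocol article*

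**What the plan says.** All references are to the protocol article.

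- **Section 2.7.2 (procedure).** Habituation, acquisition and extinction take place on the first day. A recall session follows 24 h later, at which "the same blue door (CS+) will again be presented without any aversive stimulus".
- **Section 2.8.2 (analysis).** The opening sentence names four stages and one model: "Habituation, fear acquisition, extinction, and recall will be assessed through Skin Conductance Response (SCR) amplitudes using a 2 × 2 × 3 mixed-design ANOVA". The next sentence defines the within-subject factor as "phases (habituation, fear acquisition, fear extinction) as a within-subjects factor". The ANOVA of subjective ratings has the same three levels.
- **Section 2.2.2 (sample size).** The primary test has the factor "time (3 SCR measurements: habituation, acquisition, extinction recall", crossed with CS+ and CS−, which makes six repeated measurements.
- **Section 3.2 (predictions).** Hesitant participants are expected to show weaker extinction learning, "leading to increased fear retention during the recall session".

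**The concern.** Four stages cannot be the levels of a three-level factor. In 2.8.2 the stage left out of the list is recall. In 2.2.2 it is extinction, or extinction has been merged with recall. The primary test of Experiment 2 therefore has two definitions, and they answer different questions.

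Two things are at stake. First, an analyst who follows the levels in 2.8.2 runs no test of the recall prediction, although participants return on a second day to provide those data. The Tukey comparisons follow up the same ANOVAs, so they cannot reach recall either. Second, either triple, or a four-level model, could be chosen after the data are seen and still be described as the plan.

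A related mismatch concerns the stimuli. The 2.2.2 model needs CS+ and CS− responses at recall, and 2.7.2 describes only the CS+ there.

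**Working it through.** **1. The stages side by side**

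| Stage | Procedure (2.7.2) | Opening sentence of 2.8.2 | SCR and rating factor levels (2.8.2) | Power model (2.2.2) |
|---|---|---|---|---|
| Habituation | yes | yes | yes | yes |
| Acquisition | yes | yes | yes | yes |
| Extinction | yes | yes | yes | not separately |
| Recall, 24 h | yes | yes | no | yes, as extinction recall |
| Count | 4 | 4 | 3 | 3 |

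The rest of section 2.8 gives correlations, hierarchical regressions and general between-group comparisons. None of them names recall.

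**2. Cells that need data.** The 2.2.2 model needs 2 stimuli × 3 phases = 6 measurements per participant. A four-phase model needs 2 × 4 = 8. If the CS− were not shown at recall, one cell would be empty in each: 5 of 6, or 7 of 8.

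**3. Does the choice of triple alter the stated sample size?** Inputs from 2.2.2: f = 0.25, α = 0.05, target power 0.95, r = 0.5, ε = 1, k = 2 groups, m = 6 measurements, stated N = 40. For the within–between interaction in the G*Power parameterisation:

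λ = f² N m / (1 − r), df1 = (k − 1)(m − 1), df2 = (N − k)(m − 1).

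- As stated (k = 2, m = 6, N = 40): λ = 0.0625 × 40 × 6 / 0.5 = 30, df = 5 and 190, power 0.9945. The smallest N for 0.95 is 28, so 40 is not reproduced. It comes out (power 0.9516) with k = 4 in place of the stated 2. That is a separate question and nothing here depends on it.
- Both triples give m = 6, so this calculation is identical whichever is meant.
- Four phases (m = 8, N = 40): λ = 0.0625 × 40 × 8 / 0.5 = 40, df = 7 and 266, power 0.999, required N = 24.
- CS+ only over four phases (m = 4, N = 40): λ = 20, df = 3 and 114, power 0.97, required N = 36.

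**4. A single recall comparison (illustration; the effect sizes are assumptions).** Take the group difference in CS+ minus CS− at recall, 20 per group, complete attendance, unadjusted two-sided t-test. With r = 0.5 the SD of the difference is SD × √(2 × (1 − 0.5)) = SD. The noncentrality is d × √(20 × 20 / 40) = 3.162 d, on 38 df.

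| Assumed d | Noncentrality | Power |
|---|---|---|
| 0.5 | 1.58 | 0.34 |
| 0.8 | 2.53 | 0.69 |
| 1.0 | 3.16 | 0.87 |

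The generic interaction calculation therefore says little about a focused recall test. This is why power should be restated for the model chosen.

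**The case against.** The strongest reply is that recall has not been forgotten. The opening sentence of 2.8.2 includes it, and 2.2.2 makes it a level of the primary test. The extinction hypothesis in the abstract and the aim in the Introduction concern acquisition and extinction, which the levels in 2.8.2 cover. A fuller analysis plan might settle the rest. Most of this stands. It shows that the fault is a contradiction and not a plain omission, but it does not remove the fault, because the article gives two incompatible definitions of one primary test.

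Four stronger readings are tempting, and the documents do not support them:

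- **That the retention hypothesis cannot be tested, or has zero power.** Recall data are planned, and the prediction becomes testable once the factor is reconciled. A zero-power claim takes one side of a contradiction as the plan.
- **That the CS− is absent at recall.** This would be inferred from silence. Section 2.7.2 is equally silent on the CS− at extinction, where 2.8.2 analyses both stimuli; 2.2.2 crosses both stimuli with recall; and 2.7.2 has participants rate each stimulus throughout.
- **That "conducted over one day" is wrong.** It describes the three first-day phases. Recall is introduced separately, 24 h later.
- **That a recall comparison must be adjusted for late acquisition.** Section 3.2 also predicts a group difference in acquisition, so adjusting for it changes the question. It is optional. The power figures above are unadjusted and would not apply to an adjusted contrast.

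**Conclusion.** The point holds as an inconsistency in the definition of the primary SCR analysis, repeated in the ratings analysis. Under the levels listed in 2.8.2, one of four stages (recall) enters no specified test and the retention prediction in 3.2 goes unexamined. Under those in 2.2.2, extinction is not analysed separately. The discrepancy between the triples has no numerical effect on the power calculation, since both have six measurements.

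The conclusion rests only on the wording of 2.2.2, 2.7.2, 2.8.2 and 3.2. The illustrative power of 0.34 to 0.87 for a single recall comparison rests on assumed effects of d = 0.5 to 1.0, and the conclusion does not depend on it. Whether the CS− is presented at recall is an open question for the authors and not an established design fault.

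**What to change.** 1. Use one set of phases in 2.2.2 and 2.8.2, for SCR and for ratings. Either:
   - make phase a four-level factor (habituation, acquisition, extinction, recall), giving a 2 × 2 × 4 ANOVA; or
   - keep the three-level ANOVA of habituation, acquisition and extinction, and add one separate pre-specified recall test: the group difference in CS+ minus CS− at recall.
2. Restate the power calculation for the model chosen. If a single recall comparison carries the retention hypothesis, give its power under a stated effect size.
3. Reconcile 2.7.2 with 2.2.2 by stating whether the CS− is presented at recall. If it is, either option works. If it is not, the crossed 2 × 2 × 4 model has an empty cell, so the recall test must be defined on the CS+ alone, for example relative to the habituation CS+ response. The article should then acknowledge the weaker interpretation: the habituation response accounts only partly for general reactivity, so retained conditioned fear is less cleanly isolated.

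The cost is a change of wording, slightly more analysis and at most one additional pre-specified test. No new session is needed, since recall is already scheduled. The change should be made before the data are examined, so that the choice of levels cannot depend on the results.

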#### 2.1.1. Participants

A total of 40 healthy participants, aged 18 to 50 years, will be recruited for a randomized-controlled study and categorized based on their attitudes toward COVID-19 vaccination:Vaccine-Hesitant/Resistant Group (*n* = 20): Individuals reluctant to receive the COVID-19 vaccine, identified using validated psychometric tools, including the Vaccine Hesitancy Scale [26] and the Vaccine Hesitancy Scale for COVID-19 Vaccination [27].Vaccine-Accepting Group (*n* = 20): Individuals who are vaccinated or express no hesitation toward vaccination. They will serve as controls.

Recruitment will be conducted through online advertisements and university mailing lists. To ensure comparability, groups will be matched by demographic variables, including age, gender, and educational level.

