Pearson’s or Spearman’s correlations (depending on normality) will examine associations between psychometric measures (i.e., disgust sensitivity, anxiety) and neurophysiological markers (MEPs, SCR, EMG). To address inflated Type I error rates due to multiple comparisons, all correlation analyses will be corrected using Bonferroni correction. This method adjusts the family-wise error rate by dividing the overall significance threshold (α = 0.05) by the number of comparisons performed. Hierarchical regression models will assess whether psychological variables are associated with physiological responses. Associations with VH will be explored through between-group comparisons.

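### Holm's step-down would control the same family-wise error as the planned Bonferroni correction of the correlations and never reject less: an optional, cost-free refinement of a secondary analysis

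*Protocol article*

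**What the plan says.** The last paragraph of section 2.8.2 (under 2.8, Statistical Methods) plans correlations between psychometric measures and the physiological markers: "Pearson’s or Spearman’s correlations (depending on normality) will examine associations between psychometric measures". Disgust sensitivity and anxiety are the traits it names; MEPs, SCR and EMG are the markers.

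The reason for adjusting is given as "To address inflated Type I error rates due to multiple comparisons". The method is named ("all correlation analyses will be corrected using Bonferroni correction") and so is the rule: "dividing the overall significance threshold (α = 0.05) by the number of comparisons performed". No other reason for choosing Bonferroni is given, and no simultaneous confidence intervals are planned. The number of comparisons and the expected size of the correlations are not stated.

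Sections 2.1.2 and 2.2.2 size each experiment at 40 participants on a mixed ANOVA. The article makes no power claim for the correlations.

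**The concern.** The article names a specific single-step procedure, so this is a choice it has fixed. Its only stated aim is control of Type I error over the family. Holm's procedure meets that aim equally well, and its rejections always include those of Bonferroni. On the article's own criterion, Bonferroni can therefore be improved upon at no cost in error control.

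What is at stake is power in an analysis that has little to spare. With 40 participants and a threshold of 0.05/m, a correlation must be about 0.54 (12 tests) to 0.59 (48 tests) to be found with 80% power. That limit comes from N and m and is not the cost of Bonferroni relative to Holm. It does explain why power available without loss of error control is worth taking.

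**Working it through.** **Inputs from the article.** Family-wise α = 0.05; per-test threshold 0.05/m (section 2.8.2); N = 40 per experiment (sections 2.1.1 and 2.2.1); correlation 0.5 among repeated physiological measurements (sections 2.1.2 and 2.2.2).

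**Assumptions, because the article gives no figure.** Two-sided tests on all 40 participants; m from 12 to 48; true trait-physiology correlation r of 0.3 or 0.5.

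**Step 1: the planned error rate.** By the Bonferroni inequality the family-wise error is at most m × 0.05/m = 0.05 under any dependence. If the tests were independent and all nulls true, it would be 1 − (1 − 0.05/m)^m. For m = 12 this is 0.0489, against 1 − 0.95^12 = 0.460 without correction. The article's 5% is reproduced.

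**Step 2: the two rules.** Bonferroni compares every p-value with 0.05/m. Holm orders the p-values, compares the smallest with 0.05/m, the next with 0.05/(m − 1), and so on, and stops at the first failure. For m = 12 Holm's first three thresholds are 0.00417, 0.00455 and 0.00500; Bonferroni stays at 0.00417. Two consequences follow:
- No Holm threshold is below 0.05/m, so Holm rejects everything that Bonferroni rejects.
- The first threshold is the same, so the chance of at least one rejection is identical.

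**Step 3: smallest detectable correlation under Bonferroni, 80% power.** r = tanh[(z(1 − 0.05/2m) + z(0.80))/√37], where 37 = 40 − 3. This gives 0.544 (m = 12), 0.568 (m = 24) and 0.590 (m = 48).

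**Step 4: power per true correlation.** Under Bonferroni, power is approximately Φ(atanh(r)·√37 − z(1 − 0.05/2m)). For m = 12, z = 2.865:
- r = 0.5: 0.5493 × 6.083 = 3.341, so power is Φ(0.476) = 0.68.
- r = 0.3: 0.3095 × 6.083 = 1.883, so power is Φ(−0.982) = 0.16.

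Holm's average power depends on the other p-values and was simulated with N = 40, physiological measures intercorrelated 0.5, and each real trait correlated r with every measure.

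| Family | Real associations | r = 0.5: Bonferroni → Holm | r = 0.3: Bonferroni → Holm |
|---|---|---|---|
| 2 traits × 6 measures (12) | all | 0.69 → 0.82 | 0.162 → 0.192 |
| 2 × 12 (24) | all | 0.61 → 0.75 | 0.111 → 0.128 |
| 2 × 6 (12) | one trait of two | 0.68 → 0.72 | 0.161 → 0.175 |
| 8 × 6 (48) | half the traits | 0.52 → 0.55 | 0.077 → 0.080 |
| 8 × 4 (32) | two traits of eight | 0.56 → 0.58 | 0.098 → 0.100 |

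The gain is 2 to 14 points at r = 0.5 and 0.2 to 3 points at r = 0.3. Simulated family-wise error stayed below 5% for both methods in these scenarios.

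**Step 5: sparser truth.** With 12 tests at r = 0.5, one trait related to only three of six measures gives 0.675 → 0.690, a gain of 1.5 points. With independent tests and a single real correlation, the gain is at most about 0.1 point.

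**The case against.** The strongest reply is that nothing in the plan is wrong. Bonferroni is prespecified, standard, correctly described and valid under any dependence. This stands in full: the point is an improvement and not a correction of an error.

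Four further objections also stand, wholly or in part.

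- **The correlations are secondary.** Both sample sizes rest on the ANOVAs, whose results do not depend on this choice.
- **The large gains need strong assumptions.** A reader might take the expectation in section 2.2.2, "expected consistency in responses influenced by individual differences in disgust sensitivity and anxiety", to mean that most tested correlations are real and strong. It does not say so. That sentence supports the correlation of 0.5 among six SCR measurements; it gives no trait-physiology effect size and does not concern MEPs or facial EMG. The design points the other way for some measures. The extensor carpi radialis is a control muscle, and CS− and habituation are reference conditions. Section 2.7.2 also excludes high scorers on the anxiety inventory, which tends to weaken correlations with anxiety.
- **Bonferroni has some advantages.** Its threshold for each test does not depend on the other p-values, and it yields simple matching simultaneous intervals. Since the article plans no such intervals, little would be lost here.
- **Most missed correlations would be missed anyway.** At r = 0.3, power is at most about 0.19 under either method in the scenarios examined.

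The suggestion that the choice is purely a matter of taste does not stand. For the one purpose the article states, Holm does the same job and never rejects less.

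**Conclusion.** The point holds as an optional refinement. The planned correction is valid, but Holm gives the same 5% family-wise guarantee with at least as many rejections.

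The gain in average power per true correlation is about 0 to 3 points at r = 0.3 and about 2 to 14 points at r = 0.5. This rests on N = 40, 12 to 48 tests and physiological measures intercorrelated 0.5; the family size and the true correlations are assumptions. Gains of 13 to 14 points arise only when every tested correlation is real at 0.5, and the gain all but disappears when only one is.

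A reader might infer that the plan misses true correlations for no benefit, or that its conclusions are compromised. The documents do not support either. The chance of finding at least one correlation is unchanged, no primary analysis is touched, and the main limits on power are the 40 participants and the number of tests.

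**What to change.** In the last paragraph of section 2.8.2, replace Bonferroni by Holm over the same family of m correlations: compare the smallest p-value with 0.05/m, the next with 0.05/(m − 1), and so on, stopping at the first failure. Report Holm-adjusted p-values, that is, the j-th smallest p-value multiplied by (m − j + 1), made non-decreasing along the ordering and capped at 1. The same rule serves Pearson and Spearman tests, since it uses only the p-values.

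The cost is one sentence and a different adjustment of the same p-values, with no new data and no loss of error control. Thresholds would then depend on the other p-values, and simple matching simultaneous intervals would not be available. The change is best made before the data are seen. Leaving Bonferroni in place would also be acceptable.
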